## Abstract

**Background:**

Frailty is a reversible geriatric syndrome marked by diminished physiological reserve and heightened vulnerability. In elderly patients with chronic kidney disease (CKD), frailty accelerates decline and mortality, yet individualized risk stratification and management remain limited by resource-intensive geriatric assessment and incomplete data. Integrating causal learning and model knowledge distillation may enable precision modeling of frailty risk and clinically meaningful decision support.

**Methods:**

This multicenter bidirectional cohort study (ChiCTR2500095133) will recruit 1500 adults aged ≥ 60 years with CKD (KDIGO criteria) from seven Beijing centers. Collected data will include routinely available clinical indices (demographics, medical history, anthropometric measures and laboratory tests) and resource-intensive non-clinical indices derived from comprehensive geriatric assessment (frailty, cognitive, functional, nutritional, and psychological assessments). Frailty will be assessed using the FRAIL scale. Causal feature learning will identify determinants of frailty risk, while a teacher-student knowledge-distillation framework will optimize prediction using routinely available clinical data. Internal and external validation will examine model accuracy, interpretability, and clinical applicability.

**Discussion:**

By combining comprehensive clinical assessment with advanced artificial-intelligence methods, this study aims to develop an explainable, efficient tool for early frailty detection and individualized intervention decision support in elderly CKD. The resulting framework may enhance precision geriatric management, improve functional outcomes, and reduce healthcare burden.

**Trial registration:**

Chinese Clinical Trial Registry: ChiCTR2500095133 (registered 2025-01-02).

**Supplementary Information:**

The online version contains supplementary material available at 10.1186/s12877-026-07143-0.

## Background

With population aging accelerating, CKD has emerged as a global health priority, affecting 8–16% of adults and up to nearly 40% of older adults [1, 2]. Frailty, defined as a state of reduced physiological reserve and resilience, is a frequent and severe CKD comorbidity, significantly worsening disability, hospitalization, and mortality [3–6]. Prevalence studies report frailty in 20–50% of older CKD populations [7], driven by metabolic derangements, inflammation, sarcopenia, and multimorbidity [8–10].

Frailty in CKD is clinically important yet potentially reversible [11–13]. Multicomponent interventions combining nutrition, exercise, and psychosocial support have demonstrated benefit, but personalized decision frameworks remain underdeveloped [14–17]. Current screening tools, such as Fried’s phenotype or the FRAIL scale, offer population-level risk estimation but limited mechanistic insight or individualized guidance [18–21].

Artificial-intelligence (AI) methods now offer novel avenues for precision frailty management [22–25], particularly through causal learning and knowledge distillation. However, in routine nephrology practice, non-clinical indices derived from comprehensive geriatric assessment are often unavailable because of resource and workforce constraints, highlighting the need for scalable modeling strategies that can operate under incomplete data conditions. Causal learning disentangles interdependent disease mechanisms, revealing modifiable determinants rather than mere associations [26–28]. Knowledge distillation enables translation from complex multimodal teacher models to lightweight “student” models deployable in clinical settings [29–31]. Applying these methods to CKD-related frailty may bridge data-driven discovery with explainable, clinically actionable models.

This study aims to integrate geriatric assessment with AI-based causal reasoning to (1) identify key frailty-related factors in elderly CKD, (2) develop predictive and interventional-support models using causal learning and model distillation, and (3) evaluate potential real-world clinical feasibility and applicability of the proposed framework.

## Methods

### Study design

A multicenter bidirectional cohort study is being conducted from December 1, 2024, to December 31, 2028 (Fig. 1). Beijing Chaoyang Hospital serves as the coordinating center, with six participating sites across tertiary and community hospitals. Both retrospective data extraction and prospective recruitment will be employed to establish a bidirectional cohort integrating hospital and community populations. Ethical approval has been obtained from the Institutional Review Board of Beijing Chaoyang Hospital (No. 2024-Science-914). All participants will provide written informed consent. The trial adheres to the Declaration of Helsinki and SPIRIT 2023 guidelines.

**Fig. 1 Fig1:**
[figure not shown]
Study flow diagram of the multicenter bidirectional cohort and AI-based frailty modeling framework

### Participants

#### Inclusion criteria

Age ≥ 60 years; Diagnosis of CKD per KDIGO 2024 criteria (GFR < 60 mL/min/1.73 m² or structural abnormality > 3 months); Capacity and willingness to provide informed consent.

#### Exclusion criteria 

Life expectancy < 6 months (e.g., advanced malignancy); Severe hearing or cognitive impairment precluding assessment.

### Sample size justification

The target sample size is 1,500 participants, based on both prediction-modeling and prevalence-precision considerations. Assuming a frailty prevalence of 20% [3, 7] and approximately 30 candidate predictors, the events-per-variable (EPV) rule (≥ 10) [32, 33] yields the minimum required sample:$$\:n=\frac{10\times\:30}{0.20}=\mathrm{1,500}$$

This ensures adequate frailty events (~ 300) for stable model estimation. Additionally, applying the binomial precision formula for a single proportion,$$\:n=\frac{{z}_{1-\alpha\:/2}^{2}p(1-p)}{{m}^{2}}$$

a total of 1,500 participants provides ± 2% precision (95% CI) around a frailty prevalence of 20%, which is acceptable for multi-center estimation. The chosen size thus satisfies both statistical and practical requirements for developing and externally validating a robust, interpretable prediction model.

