### Validation and evaluation

Internal validation, 70% of data used for model training and 30% for testing within the Chaoyang Hospital dataset. External validation, independent testing using data from six partner centers. Performance metrics, AUC, calibration curve, Brier score, and decision-curve analysis. Model explainability, assessed using SHAP-based feature attribution and causal-effect visualization to ensure interpretability and clinical credibility.

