## Discussion

Frailty in elderly CKD represents a dynamic, modifiable continuum rather than a fixed state [11–13, 34, 35]. Traditional assessments fail to capture individualized causal pathways linking renal dysfunction, inflammation, and functional decline [18–21]. By employing causal learning, this study aims to move beyond purely associative modeling toward improved mechanistic interpretability and clinically meaningful risk stratification [26–28], while knowledge distillation is expected to enhance scalability and applicability of the prediction framework in routine clinical settings with heterogeneous data availability [29–31].

This framework is designed to address real-world heterogeneity in frailty assessment availability across different healthcare settings. Comprehensive geriatric assessment is resource-intensive and not uniformly implemented across hospitals with different service capacities; consequently, many older patients with CKD lack complete geriatric assessment data and are often evaluated using routine clinical indicators only. To address this practical constraint, the proposed teacher–student framework is designed to extend frailty screening and intervention decision-support to data-limited clinical environments. The teacher model leverages comprehensive multimodal data when available, whereas the student model is optimized to operate using routinely collected laboratory and clinical variables. This design enables frailty screening and risk stratification under incomplete data conditions and supports broader applicability across healthcare settings with variable resource availability. In addition, the multicenter study design facilitates model development across heterogeneous CKD populations with different disease severity and comorbidity profiles, further supporting adaptability in diverse clinical environments.

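### The roughly 300 events and EPV of 10 claimed for model estimation count all 1,500 participants, but the model is trained on 70% of one centre's data, giving at most 210 events and EPV 7.0 at the assumed 20% prevalence

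*Protocol article*

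**What the plan says.** The Sample size justification of the protocol article gives two grounds for the total: "The target sample size is 1,500 participants, based on both prediction-modeling and prevalence-precision considerations". The modelling ground is the EPV rule with a minimum of 10, about 30 candidate predictors and an assumed frailty prevalence of 20%, which gives n = 10 × 30 / 0.20 = 1,500. The section then states: "This ensures adequate frailty events (~ 300) for stable model estimation". It adds that this size is enough both to develop the model and to validate it externally.

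The abstract makes clear that 1,500 is the total over all sites: the study "will recruit 1500 adults aged ≥ 60 years with CKD (KDIGO criteria) from seven Beijing centers". Under Recruitment and data collection, every centre contributes prospective data, and only the coordinating centre (Chaoyang) also contributes retrospective data. No number or share per centre is given.

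Validation and evaluation sets the data split: "70% of data used for model training and 30% for testing within the Chaoyang Hospital dataset". Data from the six partner centres are kept for independent external testing.

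**The concern.** The two sections assign the same patients to different jobs. The sample size formula treats every participant as development data. The validation plan removes the six partner centres and 30% of Chaoyang from development, and the formula has no term for data held back in this way. The 300 events are therefore expected in the study as a whole, not in the data that estimate the model.

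The EPV calculation is the only modelling argument for the sample size; the precision calculation supports a prevalence estimate, not a prediction model. If training events are far fewer than stated, a model with 30 or more parameters may be overfitted, and its predicted risks may be poorly calibrated in the decision-support tool for which it is intended. A reader would also be misled about how much information supports the model.

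**Working it through.** **Inputs.** Total N = 1,500, prevalence p = 0.20, about 30 predictors and target EPV 10 (Sample size justification); training fraction 0.70 of Chaoyang only, partner centres external (Validation and evaluation). Chaoyang's share s of the 1,500 is not stated, so it is varied from 1/7 (equal split over seven centres) to 1 (an upper bound that leaves no external data).

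**Step 1: the plan's own figure.** 10 × 30 / 0.20 = 1,500. Events: 1,500 × 0.20 = 300. EPV: 300 / 30 = 10. This reproduces exactly, provided that all 1,500 are used for fitting.

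**Step 2: the split as described.** Training events = 1,500 × s × 0.70 × 0.20 = 210 × s. EPV = 210 × s / 30 = 7.0 × s. Predictors supportable at EPV 10 = 21 × s. External events = 300 × (1 − s).

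| s | Chaoyang N | Training N | Training events | EPV | Predictors at EPV 10 | External events |
|---|---|---|---|---|---|---|
| 1/7 | 214 | 150 | 30 | 1.0 | 3 | 257 |
| 0.3 | 450 | 315 | 63 | 2.1 | 6 | 210 |
| 0.5 | 750 | 525 | 105 | 3.5 | 10 | 150 |
| 0.7 | 1,050 | 735 | 147 | 4.9 | 14 | 90 |
| 1 | 1,500 | 1,050 | 210 | 7.0 | 21 | 0 |

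**Step 3: what EPV 10 would need.** At 20% prevalence and 30 predictors, training needs 1,500 patients, so Chaoyang alone needs 1,500 / 0.70 ≈ 2,143. That is 143% of the whole study.

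**Step 4: sensitivity to prevalence.** EPV 10 requires 1,500 × s × 0.70 × p = 300, so s = 300 / (1,050 × p). With s = 1 this gives p = 300 / 1,050 = 28.6%. Above that, the required share is 0.95 at 30%, 0.71 at 40% and 0.57 at 50%. The Background cites 20–50% for older CKD populations; the sample size uses 20%.

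**Step 5: the other justification.** Half-width at N = 1,500 and p = 0.20: 1.96 × √(0.20 × 0.80 / 1,500) = 0.0202, which agrees with the stated ±2%.

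**The case against.** **Prevalence may be higher.** This stands in part. A reader might infer that EPV 10 is out of reach whatever happens. The documents do not support that: within the cited 20–50% range it is reachable above about 28.6%, if Chaoyang supplies a large enough share. The plan assumes 20%, however, and states no share.

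**Overfitting is not established.** This stands. A reader might infer that the model will be overfitted and its risks too extreme. In simulations with 30 predictors, 20% prevalence and a true AUC of 0.75 (an assumption), an unpenalised logistic model had a mean calibration slope of about 0.62 with 105 training events and about 0.85 with 300. With cross-validated ridge fitting and equal predictor effects, a setting that favours ridge, the mean slopes were 1.06 and 1.02. The article plans neither model, but an encoder, a factorisation, a causal mask and distillation. The consequence depends on the fitting method.

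**Safeguards exist.** Calibration, Brier score and decision curves are to be assessed, including in the partner centres, and deployment follows validation under physician supervision. Poor calibration should be visible before use. This limits the harm but does not correct the stated figure.

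**Retrospective Chaoyang cases might add data.** Nothing says that they come on top of the 1,500.

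**Two side issues add little.** A reader might see a contradiction in the Discussion's remark that "the multicenter study design facilitates model development across heterogeneous CKD populations". This is general prose that does not say which centres supply training data, and it can be read to include validation. A reader might also object that the total is set at the bare minimum, but the study has no follow-up endpoints and plans multiple imputation, so attrition is not an obvious gap.

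**Level of detail.** The article prints the formula, the event count, its purpose and the split. The point is a conflict between printed statements, not something left to a fuller document.

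**Conclusion.** The point holds as an inconsistency between two sections; the arithmetic in each is correct. At the plan's own 20% prevalence and about 30 predictors, the training set holds 210 × s events and EPV is 7.0 × s. Because all centres contribute, s is below 1, so both stay below 210 and 7.0. At an even division between Chaoyang and the rest they are 105 and 3.5.

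This rests on the 1,500 including the retrospective cases, on about 30 predictors applying to the model that is fitted, and on no refit to pooled data; the article says nothing to the contrary. Fewer predictors would raise EPV, and a network with more than 30 free parameters would lower the events per parameter. EPV of 10 is itself a rule of thumb, so the result shows that the stated criterion is not met. It does not show that the model will fail.

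**What to change.** **Main change.** Replace the sentence about 300 events with the expected development-set events and EPV, given expected Chaoyang enrolment and the assumed prevalence. Limit candidate predictors to what those events support (about 10 at 105 events) and specify penalised fitting. This is a change of wording and analysis and needs no extra patients. With recruitment running to the end of 2027, it can be made before the analysis. The cost is a less favourable stated EPV and a shorter predictor list.

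**Optional improvement.** Replace the 70/30 split with resampling-based internal validation on all Chaoyang data. Development events rise to 1,500 × s × 0.20 = 300 × s, for example 150 and EPV 5.0 at s = 0.5, and the six-centre external test is kept. EPV still stays below 10 at 20% prevalence with 30 predictors, because s is below 1.

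**A trade-off for the sponsor.** Developing on all seven centres with leave-one-centre-out validation would put about 300 events into the final model. That gives EPV 10 only if the parameters really number about 30. It also gives up the untouched six-centre test set that the plan commits to, and each validation fold would train on fewer than 300 events. It is therefore a change of design, not just of wording.

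### The sample-size section concludes that 1,500 suffices for external validation, but neither of its two calculations supports that part of the conclusion

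*Protocol article*

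**What the plan says.** The abstract's Methods paragraph makes 1,500 the total over all sites: the study "will recruit 1500 adults aged ≥ 60 years with CKD (KDIGO criteria) from seven Beijing centers".

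Sample size justification names two bases for that number: "The target sample size is 1,500 participants, based on both prediction-modeling and prevalence-precision considerations".

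- **EPV.** "Assuming a frailty prevalence of 20% [3, 7] and approximately 30 candidate predictors", an EPV of at least 10 "yields the minimum required sample" of 1,500. The section adds: "This ensures adequate frailty events (~ 300) for stable model estimation".
- **Prevalence precision.** With all 1,500, the 95% interval around a 20% prevalence is stated to be ±2 percentage points.

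It then concludes: "The chosen size thus satisfies both statistical and practical requirements for developing and externally validating a robust, interpretable prediction model".

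Validation and evaluation divides the sample. Training uses 70% of the coordinating centre's data, and the other 30% is the internal test set. The partner centres are kept apart: "External validation, independent testing using data from six partner centers". The metrics are AUC, calibration curve, Brier score and decision-curve analysis.

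**The concern.** The word *thus* presents adequacy for external validation as a result of the two calculations. Neither contains a validation input: no test-set size, no test-set event count, and no target for AUC or calibration. The EPV calculation also uses every patient and every event for development. The patients it counts therefore include those whom Validation and evaluation sets aside for testing, so they are counted twice.

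The external results largely decide whether the student model, which uses routine clinical data only, is credible. The Discussion itself relies on external validation to address the uncertainty it acknowledges about that model. A reader of the sample-size section would believe that the precision of those results had been worked out. It depends on a centre split that the article does not give.

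**Working it through.** **Inputs from the article.** Total 1,500 over seven centres (abstract); prevalence 20%, about 30 predictors, EPV ≥ 10 (Sample size justification); 70/30 split within the coordinating centre and six partner centres external (Validation and evaluation).

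**Assumptions made here.** The coordinating centre's share *s* of the 1,500 is not given, so 30, 50 and 70% are used. External AUC about 0.75. For the calibration slope: true slope 1, and a normally distributed linear predictor with SD 1.0, which gives an AUC of about 0.74 at 20% prevalence.

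**1. The article's own figures reproduce.**

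- EPV: 10 × 30 / 0.20 = 1,500, with 0.20 × 1,500 = 300 events.
- Prevalence: 1.96 × √(0.20 × 0.80 / 1,500) = 0.0202, or ±2.0 points.

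**2. What each leaves for external validation.**

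- EPV: 1,500 needed for development out of 1,500 recruited leaves 0 for testing. In the other direction, if partner-centre patients are held out, fewer than 1,500 remain and the stated minimum for development is not met. One figure of 1,500 cannot deliver both at any split.
- Prevalence: this estimate can use every patient, including those in the external test set. It does not compete with validation, but has no bearing on it.

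**3. External set by assumed share.** N = 1,500 × (1 − *s*); events = 0.20 × N.

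AUC half-width (Hanley–McNeil), with A = 0.75, q1 = A/(2 − A) = 0.600, q2 = 2A²/(1 + A) = 0.643, and n1 events and n0 non-events:

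1.96 × √{[A(1 − A) + (n1 − 1)(q1 − A²) + (n0 − 1)(q2 − A²)] / (n1 n0)}

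At *s* = 50%, n1 = 150 and n0 = 600: [0.1875 + 149 × 0.0375 + 599 × 0.0804] / 90,000 = 0.000599, so the half-width is 1.96 × 0.0245 = 0.048.

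Calibration-slope half-width, from the Fisher information of the logistic recalibration model. Per patient the terms are 0.1386 (intercept), 0.0652 (cross) and 0.1342 (slope). The variance of the slope is 0.1386 / [N × (0.1386 × 0.1342 − 0.0652²)], or about 9.66 / N. At N = 750: 1.96 × √(9.66 / 750) = 0.22.

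**4. Training EPV at the same share.** Training events = 1,500 × *s* × 0.70 × 0.20; EPV = events / 30.

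| Coordinating-centre share | External N | External events | AUC half-width | Slope half-width | Training N | Training events | Training EPV |
|---|---|---|---|---|---|---|---|
| 30% | 1,050 | 210 | 0.041 | 0.19 | 315 | 63 | 2.1 |
| 50% | 750 | 150 | 0.048 | 0.22 | 525 | 105 | 3.5 |
| 70% | 450 | 90 | 0.062 | 0.29 | 735 | 147 | 4.9 |

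Upper bound: with every patient at the coordinating centre, training has 1,500 × 0.70 = 1,050 patients and 210 events, an EPV of 7.0, and the external set is empty. The two columns move against each other: a more precise external test means fewer events for training.

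**The case against.** **Nothing is miscalculated.** This stands. Both published figures reproduce; the fault lies in the inference drawn from them.

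**A condensed article may leave centre numbers and validation precision to the full protocol or analysis plan.** This stands too, and the absence of a split or a precision target is not the point here. The point is the sentence that the article does print: it claims adequacy and shows the basis, and that basis does not support the claim.

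**Both calculations use up the sample.** A reader might infer this. It is wrong for the prevalence calculation, which may use all 1,500. Only the EPV calculation competes with the test set.

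**The external set is too small.** A reader might infer this as well. The documents do not support it: the split is unknown, and at a 30 or 50% share the set would hold 210 or 150 events.

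**At a 70% share, a calibration slope of 0.75 could not be told from 1.0.** This is a tempting reading of the 0.29 half-width, but that figure applies to a true slope of 1. With a true slope of 0.75 and 450 patients, the half-width is 0.26 for a linear-predictor SD of 1.0 (external AUC about 0.69) and 0.22 for an SD of 1.3 (AUC about 0.74). The answer depends on an assumed spread that the article does not give, so no such statement should be made.

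**Conclusion.** The external-validation part of the conclusion in Sample size justification does not follow from the calculations above it, at any centre split. By the article's own EPV rule, 1,500 is the minimum for development alone, and the prevalence precision is unrelated to model performance. That needs no assumption beyond the article's figures. The conclusion reached is that adequacy is unsupported, not that it is disproved.

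The size of what is left open does depend on assumptions (20% frailty, AUC about 0.75, true slope 1, share 30 to 70%). External precision would range from about ±0.041 to ±0.062 for the AUC and from ±0.19 to ±0.29 for the slope. The training EPV would be 2.1 to 4.9 over those shares, and cannot exceed 7.0 at any share. The point should be corrected, because the claim is explicit and its correction is cheap.

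**What to change.** Keep 1,500. In the last sentence of Sample size justification, delete the reference to external validation, or stop deriving it from the EPV and prevalence calculations. In its place state:

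- the expected numbers of patients and frailty events at the six partner centres together;
- the resulting 95% half-widths for the external AUC and calibration slope, with the assumptions used;
- beside them, the training EPV that the same split leaves after the 70% training share, so that the trade-off is visible.

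A fixed minimum number of partner-centre patients is not advised. Reserving 750, for example, would leave at most 750 at the coordinating centre and 525 for training (about 105 events, EPV 3.5). A quota also sits badly with the consecutive enrolment described under Recruitment and data collection.

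The cost is wording and a short calculation, with no extra patients. The downside is that the stated justification becomes less favourable, both for validation and for the EPV shown next to it.
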